### Sample size calculation

There are no data on training effectiveness of ISS upon which to base sample size calculations. We chose to calculate the required sample size based on experience with knowledge tests from data in previous studies [13,32]. We were planning a trial of a continuous response variable from independent control and experimental participants with one control per experimental participant. We assumed the response within the experimental and the control group to be normally distributed with a standard deviation of 24%. If the true difference in the experimental and control means was 17%, we needed to study 32 experimental participants and 32 control participants (a total of 64) to be able to reject the null hypothesis; that is, that there was no difference in population means of the experimental and control groups with a probability of (power) 80%. The two-sided type I error probability associated to test this null hypothesis was 5%.

### Sample size estimation adjusted for clustering

As the intervention was delivered in teams (clusters), observations on participants in the same team were likely to be correlated. Hence the effective sample size was less than that suggested by the actual number of individual participants. The reduction in effective sample size depends on the intra-class or cluster correlation coefficient (ICC) [57,58]. In order to adjust the sample size for this, the crude sample size calculated above needed to be multiplied by the design effect. The cluster size was ten, as there were ten participants in each team, and we assumed the ICC to be 0.05 [58]. Design effect = 1 + (cluster size – 1) × ICC → design effect = 1.45. Accordingly, the sample size was then 64 × 1.45 = 92.8 participants. We therefore planned to include 100 participants in the experimental and control groups (50 in each group) each of which consists of five teams of 10 participants in each arm. Statistical methods for the primary and exploratory outcome of the hypotheses are laid out in Table 2, and also the statistical methods are described. The intervention was delivered in teams, which means that participants were clustered within teams. Since observations from individuals in the same team are potentially correlated we will use generalized estimating equations (GEE) [59] in the parametric analyses to take this cluster effect into account. The statistical analysis will be adjusted for health-care professional groups. The experimental group (participants or teams in ISS) will be compared against the control group (participants or teams in OSS) for all analyses. The results will be expressed by means with standard deviations and confidence intervals, as well as by medians with percentiles. Associated *P*-values and effect sizes will be reported.

For the interval scale data, linear regression will be used to analyze changes between the experimental and the control group from baseline to peak. GEE will be used to take the clustered nature of the data into account. Non-parametric statistical analyses will be used for the ordinal scale data. Medians and percentiles will be reported and the Mann–Whitney U test will be used. Individual responses to the evaluation questionnaire are measured on a Likert scale and will be treated as ordinal data and analyzed at the item level.

To take missing data into account, all analyses will be performed as intention-to-treat analyses. Missing data will be handled by multiple imputation techniques. For all tests, we will use 2-sided *P*-values with alpha < 0.05 being the level of significance. We will use the Benjamin-Hochberg method to adjust for multiple testing [60].

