### Participants

All health-care professionals from the department of obstetrics and anesthesia, Juliane Marie Centre for Children, Women and Reproduction, Rigshospitalet, working on or in relation to the labor ward, were eligible for inclusion in the trial. These health-care professional groups, who were working on shift, encompassed: specialized obstetricians; trainee obstetricians; midwives; specialized midwives; auxiliary nurses; specialized anesthesiologists; trainee anesthesiologists; nurse anesthetists; and surgical nurses. Participants gave informed consent. Exclusion criteria were lack of informed consent, employees with managerial and staff responsibilities, staff members involved in the design or conduction of the trial, and finally employees who did not work in shifts.

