**Primary outcome**				
Multiple choice questions	Improvement occurs in the experimental group	Percentage correct in 40 multiple choice questions	Will be analyzed as interval data, a Gaussian distribution is expected	Parametric techniques
				ANOVA

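### GEE is planned on only ten teams with no small-sample method stated; in its usual form the 5% test of the primary outcome would run at about 12%

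*Protocol article*

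**What the plan says.** The primary outcome in Table 2 is "Percentage correct in 40 multiple choice questions", listed under parametric techniques with ANOVA as the named test. The statistical methods sit in the section on sample size adjusted for clustering. There the article commits to GEE for such outcomes: "Since observations from individuals in the same team are potentially correlated we will use generalized estimating equations (GEE) [59] in the parametric analyses".

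The same section fixes the number of clusters: two groups of 50, "each of which consists of five teams of 10 participants in each arm". That makes ten teams in all. It also states "The statistical analysis will be adjusted for health-care professional groups". The sample size rests on "we assumed the ICC to be 0.05" and "design effect = 1.45".

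The significance level is two-sided 5%, both in the sample size calculation and in the analysis text. Confidence intervals are promised alongside p-values. The article does not name the variance estimator (robust or model-based), the test (Wald or score), the reference distribution or a small-sample correction.

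**The concern.** The robust variance used with GEE is justified by a large number of clusters, not a large number of participants. Here the number that counts is five per arm. With so few, the usual robust standard error is biased downwards. Comparing the resulting statistic with 1.96 also ignores how poorly that standard error is estimated. Both faults push the same way, towards p-values that are too small and intervals that are too narrow.

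The stake is the primary comparison and the other individual-level outcomes that Table 2 lists as parametric: safety attitudes, anxiety score and salivary cortisol. The planned adjustment for multiple testing cannot repair p-values that are already too small when they enter it.

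**Working it through.** **Inputs from the protocol article:** K = 5 teams per arm, m = 10 participants per team, two-sided alpha 5%, SD 24, difference 17, ICC 0.05, 100 participants.

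**The plan's own figures reproduce.**
- Crude size per arm: 2 × (1.960 + 0.842)² × 24² / 17² = 31.3, so 32 per arm and 64 in total.
- Design effect: 1 + 9 × 0.05 = 1.45, and 64 × 1.45 = 92.8, planned as 100.

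**Size of the usual robust Wald test.**
- With equal teams the GEE arm effect is the difference between the two averages of team means.
- Let SS be the sum of squared deviations of team means from their arm average, over both arms. The unbiased variance of the difference is SS / [K(K − 1)]. The uncorrected sandwich gives SS / K². The ratio is (K − 1)/K = 4/5.
- The correctly scaled statistic follows t on 2K − 2 = 8 degrees of freedom. Rejecting when the Wald statistic exceeds 1.96 therefore has size 2 × P(t8 > 1.96 × √0.8) = 2 × P(t8 > 1.753) = 11.8%.
- The ICC cancels, because it scales numerator and denominator alike.
- By symmetry, half of this (5.9%) falsely favours ISS, against 2.5% nominal.
- Interval half-width relative to the correct one: 1.753 / 2.306 = 0.76, so 24% too narrow. Coverage is 100 − 11.8 = 88.2%.

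**Other variants.** If the sandwich variance is multiplied by f and the critical value is c, the size is 2 × P(t8 > c × √(0.8 f)).

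| Variance | Reference | Two-sided size |
|---|---|---|
| Uncorrected sandwich, f = 1 | normal | 11.8% |
| f = 10/9 | normal | 10.2% |
| f = 5/4 (Kauermann-Carroll in the balanced case) | normal | 8.6% |
| Uncorrected sandwich, f = 1 | t, 8 df | 7.3% |
| f = 25/16 (leverage-squared, Mancl-DeRouen type) | normal | 6.0% |
| f = 25/16 | t, 8 df | 3.3% |
| f = 5/4 | t, 8 df | 5.0% |
| Robust score test | chi-square, 1 df | 5.6% (simulated) |
| Model-based exchangeable SE | normal | 8.6% to 12.7% (simulated) |

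**Simulation check.** Exchangeable GEE was run on ten teams of ten at ICC 0, 0.05 and 0.10, with and without nine professional groups (assumed balanced across teams). There were 2,000 runs per setting, with a Monte Carlo error of about 0.7 points. The uncorrected robust Wald test rejected in 11.0% to 13.1% of runs. The 5/4-corrected variance with t on 8 df rejected in 4.2% to 6.2%.

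**Power at 100 participants.**
- Standard error: 24 × √(2 × 1.45 / 50) = 5.78, and 17 / 5.78 = 2.94.
- Normal approximation, as in the plan: P(Z > 1.96 − 2.94) = 83.7%.
- Noncentral t on 8 df, critical value 2.306: 73.2%.

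**The case against.** The strongest objection is that the article never specifies the test that produces 11.8%. It names GEE and stops there. The choice of variance estimator and degrees of freedom is the kind of detail often left to an analysis plan, and one may exist. GEE itself is not wrong, since one acceptable remedy keeps it. The robust score test runs at 5.6% even with no added correction. Table 2 also lists ANOVA for the MCQ, so the methods sentence is not the only statement about the primary test.

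Much of this stands. A reader might infer that the trial will test its primary outcome at 12%. The document does not support that: it is silent on a correction and does not rule one out. The figure belongs to one variant, though a very common one.

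Two further inferences should be resisted:
- One might read 11.8% as the chance of falsely declaring ISS superior. It is two-sided; the share favouring ISS is about 5.9%.
- One might argue that adjusting for nine professional groups ("specialized obstetricians; trainee obstetricians; midwives; specialized midwives; auxiliary nurses; specialized anesthesiologists; trainee anesthesiologists; nurse anesthetists; and surgical nurses") gives ten mean parameters on ten clusters and so invalidates the analysis. The full robust covariance matrix would indeed be rank-deficient, but the variance of the single arm contrast can still be estimated. The simulated error rate was much the same with and without the groups.

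What the objection does not remove is that the method, the number of teams and the significance level are all stated. Several ordinary ways of combining them miss 5%. The ANOVA entry does not help either, because the methods text says the parametric analyses will use GEE to account for teams. Nor can a later plan settle the matter without consequence, because a valid test lowers the power that this article reports.

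**Conclusion.** The point holds in conditional form. GEE on ten teams, without a stated small-sample method, does not secure the stated 5%. Under the uncorrected robust Wald z-test the two-sided error is about 11.8% and interval coverage about 88%. Other common variants give about 7% to 10%. A rate near 5% requires a deliberate choice: a bias-corrected variance with t on 8 df, a leverage-squared correction, or a robust score test. The article names none of these.

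The exact figures assume equal team sizes, normally distributed team means and equal variance in the two arms. They do not depend on the ICC. The power figures do depend on the plan's own SD of 24, difference of 17 and ICC of 0.05.

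**What to change.** In the statistical text of the section on sample size adjusted for clustering, replace the bare reference to GEE with one of two specified methods, for the MCQ and all individual-level parametric outcomes:
- a linear mixed model with a random team effect and Kenward-Roger degrees of freedom; or
- GEE with the Kauermann-Carroll corrected sandwich standard error and a t reference on 8 degrees of freedom. In the balanced case this equals a t-test on team means, with exact 5% size.

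Bring the ANOVA entries in Table 2 into line with the chosen method, and settle the choice before any analysis by arm.

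The wording costs one sentence and the analysis a software option. The real cost is in precision: intervals widen, and power at 100 participants is about 73% instead of about 84% by the normal approximation. That is below the stated 80%, so the power statement should be revised to reflect ten teams and 8 degrees of freedom.

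### Individual-level ordinal outcomes get a plain Mann-Whitney U test that ignores team clustering, so their nominal 5% level is not held (exploratory outcomes only)

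*Protocol article*

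**What the plan says.** All of the following is in the protocol article.

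- **Correlation within teams.** The section on sample size adjusted for clustering says that, because training was delivered in teams, "observations on participants in the same team were likely to be correlated". It uses a team size of 10, an assumed ICC of 0.05 and a design effect of 1.45.
- **Correction for it.** The same section brings in GEE for the parametric analyses, and for no others.
- **Ordinal data.** Here the section says: "Medians and percentiles will be reported and the Mann–Whitney U test will be used".
- **Outcomes concerned.** Table 2 lists cognitive appraisal and the Intrinsic Motivation Inventory (four dimensions) at individual level, N = 100, as ordinal data with the Mann-Whitney U test. The 20 evaluation questions are also individual-level and ordinal. For them Table 2 says only that non-parametric techniques apply, so the Mann-Whitney test follows from the general sentence on ordinal data.
- **Rules for the analysis as a whole.** "The statistical analysis will be adjusted for health-care professional groups". All tests are two-sided, "with alpha < 0.05 being the level of significance", with a Benjamini-Hochberg adjustment.
- **Allocation.** The Randomization section says that participants were randomized individually, stratified by professional group and available days, and then randomized into five teams per arm.

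**The concern.** The Mann-Whitney U test takes its null distribution from independent observations. The plan says its observations are not independent and then uses the test without modification. This is a stated rule that conflicts with the plan's own premise, not a detail left to an analysis plan that is not shown.

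Individual randomization does not remove the problem. The correlation arises afterwards, from a training day shared with the same nine colleagues.

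The plain test also takes no covariate, so it cannot carry the adjustment for professional group that the plan promises.

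At stake are the P-values for motivation, appraisal and participants' evaluation. The Background presents stress and motivation as the route by which in situ training might improve learning, and expects such training to show more clearly what the organization should change. Readers will look to these outcomes for that explanation.

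**Working it through.** **1. The plan's own figures.** With SD 24, difference 17, two-sided alpha 0.05 and 80% power, the crude size is 32 per arm, 64 in total. The design effect is 1 + (10 − 1) × 0.05 = 1.45, and 64 × 1.45 = 92.8. All of these agree with the article.

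**2. Level of the unadjusted test, profession ignored.** The variance of the arm difference is larger than the test assumes by the design effect (DE), so the actual two-sided level is about 2 × [1 − Φ(1.96/√DE)].

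- ICC 0.05: DE = 1.45, 1.96/√1.45 = 1.63, level 10.4%
- ICC 0.01: DE = 1.09, level 6.0%
- ICC 0.10: DE = 1.90, level 15.5%

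**3. Allowing for stratification by profession.** Let profession explain a share p of the total variance, and suppose every team has the same professional mix (a simplification). Profession then adds nothing to the difference between arms, although the test counts it as noise. With total variance 1, a team mean has variance ICC + (1 − ICC − p)/10, while the test assumes 1/10. The ratio is 1 + 9 × ICC − p, which replaces DE in the formula. The document gives no value for p, so 0, 20% and 30% are assumptions.

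The formula was checked by simulation under the null: 2 × 5 teams of 10, 7-point data, 20,000 runs per cell.

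| ICC | Profession share p | Variance ratio | Level by formula | Level simulated |
|---|---|---|---|---|
| 0.01 | 0 | 1.09 | 6.0% | 6.1% |
| 0.01 | 20% | 0.89 | 3.8% | 3.8% |
| 0.01 | 30% | 0.79 | 2.7% | 2.8% |
| 0.05 | 0 | 1.45 | 10.4% | 10.0% |
| 0.05 | 20% | 1.25 | 8.0% | 7.5% |
| 0.05 | 30% | 1.15 | 6.8% | 5.9% |
| 0.10 | 0 | 1.90 | 15.5% | 14.5% |
| 0.10 | 20% | 1.70 | 13.3% | 12.1% |
| 0.10 | 30% | 1.60 | 12.1% | 11.2% |

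At ICC 0.05 the two effects cancel in the formula when p = 9 × 0.05 = 45%.

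**4. A test that respects teams.** In the same simulated data, a t-test on the 5 v 5 team mean ranks rejects in 4.8-5.3% of runs in every cell.

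**5. Would GEE on ranks be enough?** With five equal teams per arm, the uncorrected robust variance is 4/5 of the usual variance from team means. A robust z-test therefore rejects when |t| on 8 degrees of freedom exceeds 1.96 × √0.8 = 1.753, which has probability 11.8%. Simulation gives 11-12%.

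**The case against.** Four points can be made for the plan.

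- **Only exploratory outcomes are affected.** This stands. The primary knowledge test is on the GEE path, the sample size already carries the design effect, and the Team Emergency Assessment Measure has ten teams as its units, so a plain Mann-Whitney test suits it. But the plan gives all tests a significance level and P-values, so the exploratory label does not excuse an invalid test.
- **The ICC is borrowed.** This also stands. The 0.05 was assumed in sizing the knowledge test, and the Discussion admits that there was no prior information. No ICC is given for motivation, appraisal or evaluation. It could be smaller or larger, and the documents do not support a claim that it must be larger.
- **Stratification works the other way.** Balancing profession and then ignoring it makes the test more conservative. This offsets part of the inflation, and at ICC 0.01 it can take the level below 5%. The offset depends on an unknown share of variance, so it cannot be relied on to restore 5%.
- **Extensions exist.** A stratified rank-sum test could adjust for profession. The plan does not name one, and stratifying by profession alone would not deal with teams.

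A reader might infer that the false-positive rate is simply doubled, with about 2.6 false positives expected in 25 tests (25 × 0.104) instead of 1.25. That requires an ICC of 0.05 for every outcome and no effect of profession. It also counts 20 evaluation items for which Table 2 names no test.

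A reader might also see a conflict with "Missing data will be handled by multiple imputation techniques". How rank results are pooled over imputations is a detail commonly left to the analysis plan, so it is not part of this point.

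**Conclusion.** The rule is wrong as written and should be fixed. Its reach is limited to the individual-level ordinal outcomes, all exploratory, and it cannot change the primary conclusion.

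At the plan's ICC and team size, the nominal 5% test has a true level of about 10% if profession explains none of the variance, about 8% if it explains 20%, and about 6% if it explains 30%. The range over these shares is about 3-6% at ICC 0.01 and 11-15% at ICC 0.10. The level is therefore uncontrolled, and not inflated in every case. Benjamini-Hochberg does not help, because it needs valid P-values to start from.

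The direction of the conflict rests on the article's own text. The sizes rest on an assumed ICC, assumed profession shares, equal teams of ten and an even professional mix across teams.

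**What to change.** For individual-level ordinal outcomes, replace the plain Mann-Whitney U test with one of these:

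- rank the pooled responses, average the ranks within each team, and compare five team means with five by t-test or permutation test; or
- fit a rank or ordinal model with arm, professional group and team clustering, with an explicit small-sample correction.

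Only the second option adjusts explicitly for professional group. The first benefits from balance in the teams' composition. The article names no small-sample correction for its GEE, so a reference to the same model as for the primary outcome is not enough; the correction must be stated. State also which test applies to the evaluation items. Keep the plain Mann-Whitney test only where there is one value per team.

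The cost is a few sentences and minor programming; data and sample size do not change. P-values will usually be less favourable. The permutation test also has a floor: 10 teams split 5 v 5 in 252 ways, so the smallest two-sided P is 2/252 = 0.0079. If the Benjamini-Hochberg family were these 25 tests (4 + 1 + 20, an assumption), at least four outcomes would have to reach that floor before any was declared significant, since 0.05 × 4/25 = 0.008. The t-test on team mean ranks has no such floor.

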### Randomization

Randomization was done by the Copenhagen Trial Unit, using a computer-generated allocation sequence concealed to the investigators. The randomization was conducted in two steps. The participants were individually randomized into the experimental group (ISS) or the control group (OSS). The allocation sequence was stratified according to health-care professional groups in order to resemble authentic teams and according to the days they were available for training. After individual randomization, the participants in either group (ISS and OSS) were randomized into five teams each.

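### The Mann–Whitney test named for individual ordinal outcomes carries neither the promised profession adjustment nor any handling of teams, so its type I error is not held at 5%

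*Protocol article*

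**What the plan says.** The statistical methods stand in the protocol article under Sample size estimation adjusted for clustering, and in Table 2.

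- Profession: "The statistical analysis will be adjusted for health-care professional groups". The sentence is not limited to any class of outcome.
- Teams: "we will use generalized estimating equations (GEE) [59] in the parametric analyses to take this cluster effect into account". This is limited to the parametric analyses.
- Ordinal data: "Non-parametric statistical analyses will be used for the ordinal scale data", and then "Medians and percentiles will be reported and the Mann–Whitney U test will be used".
- Table 2 names the Mann–Whitney U test for cognitive appraisal and for the Intrinsic Motivation Inventory (four dimensions). The row for the evaluation questionnaire (20 items) says only that non-parametric techniques are used at item level, so the test reaches those items only through the general sentence in the text.
- Randomization section: "The allocation sequence was stratified according to health-care professional groups in order to resemble authentic teams". Available training days were a second stratification factor.
- All tests are two-sided at 5%, with an adjustment for multiple testing.

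**The concern.** A Mann–Whitney U test in its ordinary form has no place for a covariate or a stratum. The promise to adjust for profession and the test named a few sentences later cannot both be carried out. Profession is also a design factor: stratified allocation balances it between the arms, yet an unstratified rank test still counts the variation between professions as error. Separately, the same section expects members of a team to be correlated but gives the ordinal tests no means of allowing for it.

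At stake is the meaning of the P-values for about 25 exploratory comparisons (1 for cognitive appraisal + 4 motivation dimensions + 20 evaluation items, counting appraisal once). The multiplicity adjustment takes those P-values as valid. If they are not, it cannot repair them.

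**Working it through.** **The plan's own figures.** With SD 24%, difference 17%, two-sided 5% and 80% power, n per arm = 2 × (1.96 + 0.8416)² × (24/17)² = 31.3, rounded up to 32, so 64 in total. The design effect uses "we assumed the ICC to be 0.05" and teams of ten: 1 + 9 × 0.05 = 1.45, and 64 × 1.45 = 92.8, rounded up to 100 in the plan. These figures reproduce.

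**Variance of the arm comparison.** Scale the outcome to variance 1. Let R² be the share due to profession and ICC the share due to team. There are 5 teams of 10 per arm. If profession is balanced across arms and teams, it adds nothing to the difference between arms. The variance of an arm mean is then

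ICC/5 + (1 − R² − ICC)/50 = (1 + 9 × ICC − R²)/50.

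A test that ignores both factors assumes 1/50. The true-to-assumed ratio is 1 + 9 × ICC − R², and the type I error is approximately 2Φ(−1.96/√ratio). The error is 5% when R² = 9 × ICC.

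**Results.** The ICC of 0.05 is the protocol's sample-size assumption. R² is not in the documents and is varied here. The simulation used 20,000 runs, a 7-point outcome, 5 + 5 teams of 10, and nine professions balanced by team. The last column is a profession-stratified (van Elteren) rank test that ignores teams.

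| ICC | R² | Ratio | Mann–Whitney, formula | Mann–Whitney, simulated | Stratified, teams ignored |
|---|---|---|---|---|---|
| 0 | 0 | 1.00 | 5.0% | 5.0% | 5.0% |
| 0 | 0.1 | 0.90 | 3.9% | 4.0% | 4.9% |
| 0 | 0.3 | 0.70 | 1.9% | 2.1% | 4.9% |
| 0.05 | 0 | 1.45 | 10.4% | 9.6% | 9.4% |
| 0.05 | 0.1 | 1.35 | 9.2% | 8.7% | 10.3% |
| 0.05 | 0.2 | 1.25 | 8.0% | 7.6% | 10.8% |
| 0.05 | 0.3 | 1.15 | 6.8% | 6.5% | 11.6% |
| 0.05 | 0.45 | 1.00 | 5.0% | 4.8% | 13.4% |
| 0.05 | 0.6 | 0.85 | 3.4% | 3.1% | 16.4% |

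The break-even R² is 0.09 at ICC 0.01, 0.18 at ICC 0.02, 0.45 at ICC 0.05 and 0.90 at ICC 0.10.

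**Power with ICC 0, plain against profession-stratified.**

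- 7-point outcome, shift 0.5 SD: 66.2% v 67.9% at R² 0.1 (1.7 points); 68.1% v 79.0% at R² 0.3 (10.9 points).
- 5-point outcome, shift 0.57 of the total SD: 73.9% v 75.4% (1.5 points) and 76.6% v 84.6% (8.0 points).
- If profession is irrelevant, stratifying costs 0.8 points (74.0% v 73.2%) to 2.1 points (65.6% v 63.5%).

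At ICC 0.05 neither test holds 5% at R² 0.1 or 0.3, so a power comparison there would not be like for like.

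**Are the two omissions distinct?** Dividing the Mann–Whitney statistic by the square root of the design effect of 1.45, at ICC 0.05, gives a simulated type I error of 4.4% at R² 0 and 2.3% at R² 0.3. That correction for teams leaves the profession problem in place. A correction based on the observed variation between teams of similar make-up would absorb much of it.

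**The case against.** - **Adjustment meant for the parametric models only.** The adjustment sentence directly follows the one on GEE and may refer to those models. This is possible, but the text sets no such limit, and the next sentence speaks of all analyses. Even so read, the ordinal tests still ignore the team correlation that the section itself expects.
- **A stratified version may be intended.** The article does not say that the test is unstratified, and an analysis plan not shown could specify strata. But the article does name the test, and no stratified form or ordinal regression appears anywhere in it. Stratifying alone would also not hold 5% once teams matter.
- **Too conservative.** A reader might infer that these tests are simply too conservative, because ignoring a balanced prognostic stratum lowers the type I error. That requires independent observations. At the protocol's ICC the test is too liberal for any R² below about 0.45.
- **R² is conjecture.** This stands. Nothing in the documents says how strongly profession predicts stress appraisal, motivation or evaluation scores, and the power loss is small if R² is modest. The ICC, too, was assumed for sample size and not for these outcomes.
- **Only exploratory outcomes are affected.** This also stands and limits the weight of the point.

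**Conclusion.** The inconsistency is real: the named test cannot deliver the stated adjustment, and nothing in the plan handles teams for the individual ordinal outcomes. The type I error of these tests is therefore uncontrolled in either direction: about 2–3% at R² 0.3 with no team effect, but about 9–10% at R² 0 and 6.5–7% at R² 0.3 under ICC 0.05. The power loss against a profession-adjusted analysis, with no team effect, is about 1–2 points at R² 0.1 and 8–11 points at R² 0.3.

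The documents do not support a general claim that the tests are conservative and underpowered. The sizes rest on an assumed R², on the sample-size ICC carried over to these outcomes, and on professions being balanced across arms and teams. The primary knowledge-test analysis and the team-level outcomes are outside this point. It is a worthwhile correction to exploratory analyses, not a threat to the main result.

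**What to change.** In the statistical methods text and in Table 2, replace the Mann–Whitney U test for individual-level ordinal outcomes with one of the following:

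1. a proportional-odds (cumulative-logit) GEE with arm and professional group, clustered on team, with a small-sample correction for ten teams; or
2. a re-randomisation rank test that repeats the actual allocation, respecting profession strata and teams.

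Name the method in the evaluation questionnaire row as well. Do not substitute a van Elteren test that ignores teams: it rejects 9.4% to 16.4% of the time under the null at ICC 0.05 for R² from 0 to 0.6.

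Option 1 also gives an estimate and standard error, which the planned multiple imputation, confidence intervals and effect sizes call for. Its costs are a proportional-odds assumption and a heavy model for ten teams: a 5-point item needs 4 thresholds + 8 profession terms + 1 arm term = 13 parameters, so a rule for pooling small professional groups should be fixed in advance. Option 2 avoids that load but does not by itself supply a standard error for pooling imputations.

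Either way the cost is a few lines of text and somewhat more analysis work, with wider intervals where clustering is present. No new data are needed.
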